#### Randomization

2.3.4

Following the baseline assessment, ASHAs will be randomly allocated (1:1) to one of two study arms using Stata-17 [37]. Stata allows the researcher to set the ‘seed’ used to start the random number generator (RNG) process, so that it is reproducible; and it tracks the ‘state’ which the RNG is in before each command is run. Therefore, with each command, the RNG ‘state’ within the seed changes, which maintains the randomness of each subsequent command. Since we will train all ASHAs on HAP prior to randomization, any potential effects of mental health training on ASHAs' own wellbeing will be balanced between the arms. Prior to randomization, we will first stratify ASHAs who will complete baseline assessments using age (in years) and education level (number of total years of education), as these are some of the variables that may affect an ASHA's absorption of the intervention content and potentially affect the wellbeing outcome. Stratification will ensure that age- and education-distribution between the arms is balanced. Research team will inform all ASHAs (regardless of arm allocation) of the scheduled dates of their next (1-month) follow-up assessment, and so on for 3-month and 6-month follow-ups. Further, a separate research assistant will call the ASHAs and confirm their availability to attend the intervention residential workshop (if allocated to the intervention arm). ASHAs allocated to the intervention arm will receive the workshop within 7–10 days of baseline assessment.

#### Interventions

2.3.5

##### Routine health system support

2.3.5.1

As per National Health Mission guidelines [38], supervisors (‘facilitators’) provide support to ASHAs and ‘mentor’ them to improve their effectiveness, particularly for ASHAs who function poorly on many of their tasks or remain absent in periodic meetings/trainings. Possible reasons for poor functionality of these ASHAs include their low skill or knowledge levels, delays in payments, irregular medication supply for their services, inappropriate behaviours of health system staff, lack of family support for working, illness in the family, other social barriers, or no interest in working as ASHAs. Therefore, routine supervision will be treated as the standard of care in this trial. ASHAs in the intervention arm will receive the proposed positive psychological coaching intervention in addition to routine supervision. ASHA supervisors will not be involved in the coaching intervention activities i.e., residential workshop and remote coaching, due to hierarchical differences between supervisors and ASHAs, which can potentially affect ASHAs' reception/experiences of the intervention.

### Study measures

2.4

All questionnaires will be self-administered using paper forms overseen by research coordinators and research assistants blinded to participants’ arm allocation. All assessments will be targeted for completion within seven days of the due assessment date in each arm. For each of the baseline, 1-month, 3-month and 6-month follow-up visits, the ASHA will receive INR 300 (∼ USD 3.5) as participant compensation.

#### Primary outcome (ASHA-level)

2.4.1

Authentic Happiness Inventory (AHI) is a subjective measure for the assessment of happiness [40]. We have used the term ‘wellbeing’ to represent this specific measure of happiness (including hedonic (pleasure attainment) and eudaimonic (meaning and self-realisation) wellbeing). AHI includes 24 sets of five statements [e.g., ranging from 1 (“I feel like a failure”) to 5 (“I feel I am extraordinarily successful”)] from which, the respondent chooses the statement that best describes her feelings in the past one week. AHI has been designed for monitoring upward changes in happiness [40] and has often been used in positive psychology intervention studies [[41], [42], [43], [44]]. Internal consistency at pre-test has been reported to be high (Cronbach's α = 0.94). AHI has been validated for construct validity, and linguistically/contextually adapted for this trial. AHI will be administered at baseline, 3 months (primary outcome assessment) and 6 months (potential long-term effects on wellbeing).

#### Secondary outcomes (ASHA-level)

2.4.2

For assessing the possible explanatory variables, which could contribute to the hypothesized between-arm difference in wellbeing/authentic happiness scores at 3-month follow-up, the 20-item international Positive and Negative Affect Schedule (PANAS) Short Form (I-PANAS-SF) will be used to assess ASHA affect [45]; the ‘Flourish index’ (by VanderWeele, T.J.) including two questions from each of the five principal domains of happiness and life satisfaction, mental and physical health, meaning and purpose, character and virtue, and close social relationships, will be used to assess flourishing [46]; and the Occupational Self Efficacy Scale (OSES) will be used to assess self-efficacy [47]. These measures will be administered at baseline, 1- and 3-months. For assessing the levels of variables related to wellbeing/authentic happiness, the emotional exhaustion sub-scale of the Maslach Burnout Inventory–Human Service Survey [48], the motivation scale pretested for Indian frontline health workers [49], the 14-item Physical Health Questionnaire [50] to assess somatic symptoms (contributed by work-stress/burnout) and the health-related quality of life survey (EQ-5D) validated for the Indian population [51] will be used at baseline, 3- and 6-months.

Daily/weekly/monthly/quarterly service delivery measures (depending on the type of service and as routinely monitored by the health system) will represent a global measure of routine ASHA services (non-mental health) in terms of their contact points with the community, for example through home visits, facility contacts, and community visits. We will categorize this outcome as per the type of services, such as proportion of antenatal check-ups, vaccinations, or post-natal care visits completed out of the expected for a defined period (e.g., month or quarter, as gathered by the health system). We will collect the service delivery data from the district team from the period starting from baseline till 6-month follow-up for between arm comparisons. We will gather data on the fidelity of the routine supervision activities from ASHA supervisors of both arms as part of data collection for secondary ASHA-level outcomes to monitor the ‘standard of care’ as discussed in section 2.3.5.1 and Table-1. Besides this aspect, there is no involvement of the health system appointed ASHA-supervisors in the study or the intervention. Refer Table 2 for details on ASHA-related outcome measures.

**Primary Outcome**					
***Wellbeing***	Authentic Happiness Inventory (AHI)	Authentic Happiness Inventory (AHI) is a subjective measure for the assessment of happiness [40]. AHI includes 24 sets of five statements [e.g., ranging from 1 (“I feel like a failure”) to 5 (“I feel I am extraordinarily successful”)] from which, the respondent chooses the statement that best describes her feelings in the past one week. AHI has been designed for monitoring upward changes in happiness [40] and has often been used in positive psychology intervention studies [[41], [42], [43], [44]]. Internal consistency of 0.94 at pre-test has been reported.	We have used the term ‘wellbeing’ to represent this specific measure of happiness – AHI items represent both hedonic (pleasure attainment) and eudaimonic (meaning and self-realisation) wellbeing.	Mean AHI scores will be significantly greater in the intervention arm or among ASHAs receiving the character-strengths based coaching intervention in addition to routine supervision, compared to ASHAs receiving routine supervision alone (control arm)	Baseline, 3- and 6-month follow-up
**Secondary Outcomes**					
***Affect***	10-item international Positive and Negative Affect Schedule (PANAS) Short Form (I-PANAS-SF)	The I-PANAS is developed as a measure of the affective component of subjective wellbeing. The five positive affect (PA) states include: active, determined, attentive, inspired, and alert. The five negative affect (NA) states include: afraid, nervous, upset, hostile, and ashamed. Higher scores on both PA and NA items indicate the tendency to experience a positive and negative mood. Respondents are requested to rate the statement on a 5-point scale (not at all to extremely) by comparing themselves during the past 2 weeks with their ‘usual selves’.	I-PANAS-SF has acceptable psychometric properties such as cross-cultural stability and factorial invariance [70] and there is prior evidence of this measure being used to assess affect in other workplace employees in India [71]	Total PA and NA scores will be significantly greater and lesser, respectively, in the intervention arm relative to the control arm	Baseline, 1- and 3-month follow-up
***Flourishing***	Flourish and Secure Flourish Index (T. J. VanderWeele, T.J.)	The “Flourish” index (FI) consists of two questions or items from each of the following five principal domains: happiness and life satisfaction, mental and physical health, meaning and purpose, character and virtue, and close social relationships [46]. Each of the questions is assessed on a scale of 0–10. The FI score is obtained by adding the scores from each of these ten questions (total: 0–100). The “Secure Flourish” index (SFI) is similar to the FI, except for two additional questions on financial and material stability, which may indicate the capacity to sustain flourishing across the five principal domains. For interpretation, the FI and SFI scores are reported as averages of the questions (rather than sums), therefore all scores are scaled from 0 to 10.	The questions in FI are based on existing questions, which have received empirical validation and are widely used in studies on wellbeing. Studies have put forth the psychometric properties of both these indices [72] -evidence of validity and reliability (Cronbach's α = 0.89 for FI; Cronbach's α = 0.86 for SFI).	Mean FI and SFI scores will be significantly greater in the intervention arm relative to the control arm	Baseline, 1- and 3-month follow-up
***Self-Efficacy***	Occupational Self-Efficacy Scale	The scale consists of 19 items and uses a five-point Likert-scale with the response range varying from one for ‘strongly disagree’ and five for ‘strongly agree.’ Some sample items for this measure are ‘When confronted with a difficult task, I am willing to spend whatever it takes to accomplish it,’ and ‘I adjust quickly to challenges that come in my work.’	The scale's psychometric properties have been analysed in the Indian context [47].	Mean OSES scores will be significantly greater in the intervention arm relative to the control arm	Baseline, 1- and 3-month follow-up
***Burnout***	Emotional Exhaustion sub-scale of the Maslach Burnout Inventory–Human Service Survey	The overall questionnaire measures three burnout components: emotional exhaustion (8 items, Cronbach's α = 0.89), depersonalization (5 items, Cronbach's α = 0.69) and reduced personal accomplishment (7 items, Cronbach's α = 0.79). Emotional exhaustion is seen as the core component of this tool. Items are scored on a seven-point Likert's style scale – ‘never’ to ‘daily’ [48,57].	The Maslach Burnout Inventory (MBI) is used in most studies included in a systematic review on burnout in frontline primary health providers in low- and middle-income countries [1].	Mean MBI scores will be significantly lesser in the intervention arm relative to the control arm	Baseline, 3- and 6-month follow-up
***Motivation***	23-item structured motivation scale by Tripathy et al. (2016) for Indian rural health workers [49]	The tool has 23 items, with answers given on an agreement scale of 1–4 (1 = strong disagreement, 4 = strong agreement). Reverse coding is done for negative questions before analysis. The scale for negatively worded question is 1 (strong agreement) to 4 (strong disagreement). The tool has eight major constructs: general motivation, burnout, job satisfaction, intrinsic job satisfaction, organizational commitment, conscientiousness, timeliness and personal issues	The tool is adapted from a motivation construct developed by Mbindyo et al. which is adapted from Bennet et al. [49,73,74]. The tool has been used with community health workers in rural health facilities in India.	Mean motivation scores will be significantly greater in the intervention arm relative to the control arm	Baseline, 3- and 6-month follow-up
***Physical Health Synptoms***	14-item Physical Health Questionnaire (PHQ)	Respondents indicate how much they have been bothered by each of 14 symptoms in the past month. Response options are “not at all”, “bothered a little”, and “bothered a lot.”	Prior validation results showed that the PHQ is composed for four factors representing Gastrointestinal Problems, Headaches, Sleep Disturbances, and Respiratory Infections. The factors contributed to substantial amounts of item variance, and the PHQ dimensions demonstrated acceptable levels of internal consistency, except somewhat low for the Respiratory Infections subscale (0.66) [50].	Mean PHQ-14 scores will be significantly lesser in the intervention arm relative to the control arm	Baseline, 3- and 6-month follow-up
		*Somatic* symptom categories include gastrointestinal problems, headaches, sleep disturbances, and respiratory illness.			
		Average score is calculated for each participant.			
***Quality of Life***	EuroQol-5D and Visual Analogue Scale	The EQ-5D includes five questions on mobility, self-care, pain, usual activities, and psychological status with five possible answers for each item. The maximum score of 1 indicates the best health state, by contrast with the scores of individual questions, where higher scores indicate more severe or frequent problems. In addition, there is a visual analogue scale (VAS) to indicate the general health status with 100 indicating the best health status.	Norms for Indian population are available [51] based on a survey of 3548 adults in five states of India. The utility score was calculated using the EQ-5D-5L value set and norm scores were generated for age, sex, and other socio-demographic variables.	Mean EQ-5D and visual analogue scores will be significantly greater in the intervention arm relative to the control arm	Baseline, 3- and 6-month follow-up
***Service delivery measures***	Routine service delivery indicators as collected by the health system (e.g., related to antenatal checkups done, post-natal visits conducted, immunizations done)	A survey form will be generated with a list of routine ASHA performance indicators in consultation with the district health team. The form will include indicators for various services such as antenatal and postnatal care, reproductive health, and immunization. Examples of specific indicators include proportion of antenatal checkups expected out of total pregnant women in the ASHA's catchment area (for a fixed period e.g., a reporting month) and proportion of antenatal checkups completed out of total expected checkups.	Given the evidence-base, improved wellbeing can contribute to improved service delivery as reflected in changes in observed service delivery indicators [[65], [66], [67], [68], [69]].	Percentages of services delivered will be significantly higher in the intervention arm relative to the control arm	Data will be collected directly from the district health team for the period starting from baseline assessment to end of 6-month follow-up assessment.
		With respect to depression care, data on number of HAP sessions delivered, patients with completed treatment and patient dropouts will be gathered from ASHAs.			Number of HAP sessions delivered; number of patients with completed treatments; and number of patient dropouts will be compared between arms at 3-month and 6-month follow-up
***Cost of Intervention delivery***	Cost of ASHA's participation in the workshop (survey) and cost of participation in remote coaching (survey)	We will assess costs incurred by ASHAs due to their participation in their respective intervention workshop and remote coaching activities. A post-workshop questionnaire (on day-5) and a remote coaching questionnaire (during the 4th and 8th coaching call, covering data of the previous calls) will be developed and administered to capture individual-level costs incurred by ASHAs, such as items covering their workshop/remote coaching time, workshop travel time, workshop travel costs, smartphone data packs (remote coaching) and food/refreshment costs (residential workshop).	If the primary outcome results show significant differences in mean authentic happiness scores between arms at 3-month follow-up as seen in the pilot study (under peer review), estimating the cost of delivering such an intervention will have significance from the point of view of health system adoption.	Data only collected in the intervention arm	Post-workshop questionnaire administered to ASHAs on day-5 of each intervention workshop batch.
					Remote coaching questionnaire administered to ASHAs during the 4th and 8th coaching call, covering data of the previous calls.

With respect to depression care delivery, we will calculate the number of ASHAs’ HAP sessions, on a weekly basis. At 3-month and 6-month follow-up, we will compare the numbers of these HAP sessions between arms (Note: HAP treatment durations range from 6 weeks to 3 months), in addition to numbers of patients with closed (completed) treatments and drop-outs.

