### Study objectives and hypothesis

1.1

The objective of this two-arm randomized controlled trial is to compare the effectiveness of a character-strengths based coaching intervention on wellbeing of ASHAs relative to routine health system supervision that ASHAs already receive.

The hypotheses include:A)Primary hypothesis: ASHAs who receive the proposed coaching intervention (in addition to routine supervision) will show greater wellbeing than those who receive routine supervision alone.B)Secondary hypotheses:a)ASHAs who receive the proposed coaching intervention (in addition to routine supervision) will show greater reduction in burnout and increase in motivation scores, than those who receive routine supervision alone.b)ASHAs who receive the proposed coaching intervention will show greater improvement in service delivery indicators (e.g., daily service contacts for routine services such as prenatal check-ups and conducting brief psychological treatment sessions for depression) than those who receive routine supervision alone.c)ASHAs who receive the proposed coaching intervention will show greater patient satisfaction for depression care services, and rates of remission in their patients' depression severity at endpoint, than ASHAs who receive routine supervision alone. (Note: All ASHAs prior to baseline assessment will be trained to deliver the brief psychological treatment for depression, see Fig. 1)

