#### Participant training on the evidence-based brief psychological treatment for depression

2.3.2

In the sampling frame, we will sample a target of 330 ASHAs for orientation and training on the Healthy Activity Program (HAP), an evidence-based brief psychological treatment for community-based care for people identified with depression [29]. We will use simple random sampling (SRS) without replacement for this purpose. SRS will offer maximum sample diversity, equal chance of representation of all ASHAs, high internal and external validity and ease of data analysis [33,34]. This is about 25 % higher than the required number of ASHAs (n = 244, refer 2.6) to account for potential attrition/loss to follow-up and health workers who may decline to participate in HAP training and/or further study processes i.e., baseline assessments, intervention activities and outcome assessments (Fig. 1). The sampled ASHAs will be assigned unique participant IDs, which will be used to contact them regarding trial recruitment. These IDs will stay with the ASHAs throughout the trial period. The research team will call the sampled ASHAs from the list to invite them to participate in the study, starting with an in person orientation on the digital training platform [29] and training for delivering the HAP. After orientation and training completion, ASHAs will start community screening for depression and delivery of 6–8 HAP sessions (every ∼8–15 days) for each patient. ASHAs will also receive fortnightly peer group supervision for the delivery of HAP as documented in previous contextual studies [29,35]. A dedicated team of HAP supervisors, through the MindScroll Learning Management System [36], will supervise the ASHAs’ challenges in delivering HAP, and also retrieve the data on delivery of HAP sessions.

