From the standpoint of patient recruitment, all patients (of both arms) who score ≥10 on the nine-item Patient Health Questionnaire (PHQ-9) and have agreed to receive the first HAP session by the ASHA will be approached for participation in the study, and after obtaining written informed consent, the research team member will administer the baseline assessment (i.e., social and demographic information) to the patient. We will use the PHQ-9 score as assessed by the ASHA prior to starting HAP as the ‘baseline’, and the endline assessment including a repeat PHQ-9 and assessment of patient satisfaction, conducted by the research assistant after 3 months, will allow a comparison of pre- and post-HAP PHQ-9 scores, in addition to between-arm comparison of remission rates at follow-up.

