### Blinding

2.5

Research coordinators and research assistants administering study assessments to ASHAs and patients, will be blind to participant allocation, and study investigators (except data manager) will also be blind to participants’ experimental condition. Participants will be told their arm allocation only after consent and baseline assessment. There is complete separation between the team members involved in developing or delivering the intervention and assessing intervention fidelity and process indicator data (2.3.5.2 and 2.4.4), and the team members involved in administering the outcome assessments (2.4.1 to 2.4.3). Outcome team members and investigators will be unblinded after the completion of analysis of data of baseline, 1-, 3- and 6-month follow-up assessments.

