## Discussion

3

Our intended impact is to demonstrate improved wellbeing of frontline health workers by the delivery of a character-strengths based coaching intervention. The expected study results will position our team to propose this intervention model to be adopted by wider stakeholders. Importantly, these stakeholders include key cadres of frontline workers in India including ASHAs in other districts and states, Auxiliary Nurse Midwives who are health facility based, Aanganwadi Workers who work towards improving child nutrition and growth, as well as community health officers (CHOs) in sub-health centres. There are more than a million ASHAs in India (one of the largest community health worker programs in the world [7]) and this study would pave the way for addressing one of their most pressing challenges i.e., poor mental wellbeing and burnout. Given the evidence-base, improved wellbeing can contribute to improved service delivery with a consequent benefit to patients and communities [[65], [66], [67], [68], [69]]. Therefore, the trial is positioned to strengthen the overall primary care system by first improving the wellbeing and reducing burnout among ASHAs with the consequent improvement in delivery of their frontline services.

From the perspective of challenges at a broader level, we want to mention that post-pandemic, the government has also introduced training modules for ASHAs to make them aware of mental health conditions and coping with mental stress. While the ‘seeding’ of ASHAs by knowledge of mental health will affect all trial ASHAs, across both arms, we will consider gathering qualitative data on these aspects through the course of the trial, particularly during the focus group discussions (section 2.4.6). Another challenge could be the aspect of socially desirable response patterns in the answers provided to psychometric tools, especially given that ASHAs work at the bottom of system hierarchies. This will be addressed by standardised procedures of providing instructions to ASHAs during outcome assessment (e.g., emphasis on ‘no right and wrong answers’, standard operating procedures for outcome assessors to clarify ASHAs' queries, and providing a comfortable environment for outcome assessment).

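### HAP session, completion and drop-out counts come from ASHAs who know their arm and are compared between arms with no stated independent check

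*Protocol article*

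**What the plan says.** In the service delivery row of Table 2, the depression-care part reads "data on number of HAP sessions delivered, patients with completed treatment and patient dropouts will be gathered from ASHAs". The timeline column of that row adds that the number of sessions, the number of completed treatments and the "number of patient dropouts will be compared between arms at 3-month and 6-month follow-up". The paragraph after the table repeats this comparison and says that sessions are tallied weekly.

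Secondary hypothesis (b) in section 1.1 expects greater improvement in delivery indicators in the coaching arm. One of its examples is "conducting brief psychological treatment sessions for depression) than those who receive routine supervision alone".

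On blinding, section 2.5 says "Research coordinators and research assistants administering study assessments to ASHAs and patients, will be blind to participant allocation". The ASHAs themselves are not blinded: "Participants will be told their arm allocation only after consent and baseline assessment".

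Three other places bear on the point:

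- Section 2.3.2 describes HAP supervisors who work through the learning management system "and also retrieve the data on delivery of HAP sessions".
- Section 2.3.3 describes a patient endline assessment "conducted by the research assistant after 3 months". Section 2.4.3 lists its content as the PHQ-9, the satisfaction questionnaire and an adverse event form.
- The Discussion foresees "the aspect of socially desirable response patterns in the answers provided to psychometric tools". Its remedies are standard instructions, procedures for answering queries and a comfortable setting.

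The routine, non-mental-health indicators in the same row of Table 2 come from the district health team, not from the ASHA.

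**The concern.** The person who supplies the count knows her arm. A blinded research assistant who writes the number down does not change that. ASHAs in the coaching arm also attend a five-day workshop and have calls every week to ten days about their work. That is a plausible route to reporting that differs by arm, although the protocol contains no evidence that it does.

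Happiness and burnout can only be self-reported. Sessions delivered and treatments finished are events that a second person witnessed. The trial already sends a blinded assistant to that person at 3 months, but the listed content of the visit does not include either fact. The protocol expects socially desirable answers, yet its stated safeguards are aimed at the psychometric forms.

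At stake is the reading of the depression-care part of hypothesis (b), and of the analyses in section 2.8 that relate service delivery measures to wellbeing and burnout.

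**Working it through.** **The plan's own figure.** Section 2.6 gives AHI means 3.35 (SD 0.43) and 3.16 (SD 0.48), 90% power and two-sided α 0.05. The pooled SD is √((0.43² + 0.48²)/2) = 0.4557 and the standardised difference is 0.19/0.4557 = 0.417. The t-test solution is 121.85, so 122 per arm, as stated. The protocol gives no mean, SD or target difference for the HAP counts.

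**Inputs for the check.** n = 122 per arm (section 2.6). True effect nil. Intervention-arm counts inflated by a fraction o (assumed). Between-ASHA coefficient of variation CV (assumed, 0.5 to 1.0 for the main range). Two-sided 5% test.

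**Formula.** The spurious difference in SD units is o/CV. The expected test statistic is λ = (o/CV)·√(n/2) = (o/CV) × 7.81. The rejection rate is about Φ(λ − 1.96) + Φ(−λ − 1.96). The table uses the t-test version of this. If the intervention-arm SD grows with its mean, λ becomes o / (CV·√((1 + (1 + o)²)/n)), and the last column gives Φ(λ − 1.96), the rate in favour of coaching only.

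| o | CV | o/CV | Significant, either direction, SD unchanged | Significant in favour of coaching, SD inflated |
|---|---|---|---|---|
| 5% | 0.5 | 0.10 | 12% | 12% |
| 5% | 1.0 | 0.05 | 7% | 6% |
| 10% | 0.5 | 0.20 | 34% | 32% |
| 10% | 1.0 | 0.10 | 12% | 11% |
| 20% | 0.5 | 0.40 | 88% | 81% |
| 20% | 1.0 | 0.20 | 34% | 29% |

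Without over-reporting, the two result columns would read 5% and 2.5%.

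**Break-even.** A difference just reaches p = 0.05 at 1.96 × √(2/122) = 0.251 SD. That is 12.5% of the mean at CV 0.5 and 25% at CV 1.0. At 7 sessions per ASHA (one patient, midpoint of the 6–8 sessions in section 2.3.2), this is about 0.9 and 1.75 sessions.

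**Dependence on the CV.** If counts vary less between ASHAs, the comparison is more fragile. At CV 0.3 and 0.2, a 10% excess gives 70% and 96% (last-column method).

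**Completion as a proportion.** Assume one patient per ASHA, so 122 patients per arm, and a true completion rate of 50% to 80% in both arms. A 10-point reporting excess in one arm is significant in 35% (50% reported as 60%) to 59% (80% reported as 90%) of trials.

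**The case against.** The strongest reply is that the protocol need not rely on an unverified report at follow-up. Table 2 says whom the data come from. Section 2.3.2 says who retrieves session data and through which system. The text after Table 2 speaks of weekly counting. These can be one flow: ASHAs log sessions, supervisors retrieve them. That stands. A reader might infer a contradiction between two rival sources, or that the counts rest on recall. The documents do not support either; recall is not mentioned, and what is needed is a clarifying statement.

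A reader might also infer that the system data are an objective source already available for all three counts. This is not supported. Section 2.3.2 mentions retrieval only for session delivery, not for completion or drop-out, and nothing shows that the system data are independent of what ASHAs enter.

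Further, bias needs reporting that differs by arm; equal over-reporting creates no difference. The fortnightly HAP supervision is described without distinction by arm. The patient visit reaches only consenting patients at 3 months, and the article may not list every item on the patient form. Other parts of hypotheses (b) and (c) rest on district data and blinded patient assessments. All of this limits the weight of the point. None of it supplies a stated check on counts that Table 2 attributes to unblinded participants.

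**Conclusion.** The point holds as a bias risk on one part of a secondary outcome, open to a cheap improvement. Table 2 takes three counts from people who know their arm and compares them between arms, and no independent verification is stated.

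The size rests wholly on two assumptions: the CV, and the presence of an excess in one arm only. With a CV of 0.5 to 1.0, a 10% excess gives roughly 11–34% significant results under no true effect. At the upper end of that CV range a small excess changes little, and about 25% is needed to reach p = 0.05. It would therefore be too strong to say that modest over-reporting will create the hypothesised effect, or that a positive result could never be told apart from reporting differences. The primary outcome, its analysis and the sample size are untouched.

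**What to change.** 1. Add two items to the existing blinded 3-month patient visit: how many HAP sessions were received, and whether treatment was finished or stopped.
2. Report agreement between these answers and the ASHA-sourced counts by arm, and run a sensitivity analysis of the 3-month comparison on the patient-reported values.
3. State in Table 2 whether its counts are the supervisor-retrieved system data of section 2.3.2. Where session records made at the time of delivery exist, use them for the session counts in both arms, extracted by staff not told allocation.
4. Interpret the 6-month comparison with the caveat that it has not been verified.

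The cost is two form items, a clarified table entry and one additional analysis. Patient recall is imperfect, and coverage is limited to consenting patients reached at 3 months, so the check tests for differential reporting and does not replace the full counts.
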